### AIM #2: Implementation of a standardized OR-to-ICU handoff process

The published literature contains both tools (i.e. checklists, forms) [5, 7–9, 11, 12] and protocols (i.e. pathways, care algorithms) [7–9]
[10]
[26] used in standardized OR-to-ICU handoffs. There are common elements of both the tools and the protocols (Figure 2).

**Figure 2 Fig2:**
[figure not shown]
**Shared features of OR-to-ICU handoffs in published studies.**

#### AIM 2 procedures

On the basis of the needs assessment (Aim #1), and in conjunction with ICU clinical leadership (i.e. nurse managers, medical directors), the research team will adapt published protocols to develop a standard process incorporating the informational needs and clinical priorities of the clinicians who will employ it. This implementation process will include the development of a customized tool or checklist to facilitate information transfer. We will take care to account for the clinical priorities of disparate surgical populations, developing a tool that balances the amount of information provided (enough to facilitate care and anticipate patient needs) with the length of the instrument (not so long as to be burdensome).

Once we have developed a standardized process, we will conduct in situ (i.e. in the hospital) simulations of this process to determine whether the process, as planned, is a reasonable replacement for the current OR-to-ICU workflow. Trained staff from the Penn Medicine Simulation Center will facilitate simulation sessions to elicit feedback from participants for the candidate standardized process. Realistic manikins will be programmed to exhibit vital signs and will be connected to transport monitors so that we can closely mimic the transport process of a critically ill patient. The manikins will be transported to the ICU by clinicians from anesthesia and surgery. This mock OR team will then carry out the new handoff process with a mock ICU team consisting of an ICU registered nurse and a nurse practitioner or resident physician. During the simulated handoff, trained observers will score the interaction using the tool employed in Aim 1. After simulating the standardized process, a debriefing session will be held to elicit feedback about the process. Simulations will be video recorded and debriefing sessions will be audio recorded; we will analyze these recordings to find themes relating to intervention feasibility and provider acceptance of the proposed handoff intervention.

The full-scale implementation process will employ 4 of 6 published implementation strategy categories described by Powell *et al.*
[27] (*implementation process*)^b^. The first 3 strategies are part of Aim 2, and are described here.

Implementation Strategy 1 - Planning: The needs assessment (Aim 1) described earlier is the first part of the planning process. Once we analyze data from the needs assessment, we will share our findings with physician and nurse leaders in each ICU (“champions”). We will work with these champions to create a new handoff process that incorporates elements from published studies (Figure 2) as well as important themes emerging from the needs assessment (Aim 2). We will also work with ICU champions to troubleshoot problems with implementation. Anticipated problems with implementation include the following: tool availability and ease of use, patient physiologic instability distracting from the process, clinician familiarity with the tool and the process, and clinician reluctance to adopt a new process. The research team will take detailed field notes during planning sessions with local champions.

Implementation Strategy 2 - Education: We will hold meetings of nursing and physician staff to share the results of the needs assessment and process development and to share the plan for implementation. Clinicians’ concerns will be addressed during these meetings and recorded with field notes taken by the research team. The handoff process will be adapted to account for these concerns. The research team will develop a glossary of terms related to the handoff process that will serve as an enduring reference, and the research team will be available in- person, by telephone, and via electronic mail during the study period for consultation as needed. We have created a study website (http://www.pennhatricc.com) that will serve as an additional educational resource for clinical staff and anyone with questions related to the study.

Implementation Strategy 3 - Restructuring: We will facilitate relay of clinical data from the OR team to the ICU team by making the handoff tool part of the patient’s bedside (nursing) chart. In this way, written information will be available to supplement and reinforce the verbal information transmitted during the handoff process. We will work with our local champions to facilitate this restructuring.

#### AIM 2 measures

Given that Aim 2 precedes use of a standard handoff process, we will assess only implementation outcomes for this phase of the study.

Implementation outcome 1: Acceptability of a standard handoff process. Once findings from the needs assessment are shared with providers and clinical leadership, perceptions of our proposed intervention may change. We will assess acceptability as described above, using simulation debriefing transcripts and field notes from interactions with clinical champions.

Additional implementation outcomes: Appropriateness and feasibility, assessed qualitatively as described above.

### AIM #3: Evaluate the implementation and effectiveness of a standardized OR- to-ICU handoff process

#### AIM 3 procedures

As mentioned above, the full-scale implementation process employs 4 of 6 implementation strategy categories described by Powell *et al.*
[27] (*implementation process*). Aim 3 incorporates the fourth implementation strategy.

Implementation Strategy 4 – Quality Management: After implementation, the research team will evaluate the new handoff process using the methodology employed in the needs assessment phase. We will repeat the data collection procedures described for Aim 1 - observations, chart reviews, event report reviews, focus groups, interviews and surveys. We will use the same instruments for observations and chart reviews for Aims 1 and 3. In the focus groups, interviews and surveys for this Aim, questions and probes will elicit impressions about the new handoff process, including feasibility and acceptance of the new process.

The results of these assessments will be shared with clinical staff via meetings and poster boards in each ICU. After the initial evaluation period, we will evaluate 10 handoffs monthly for one year to test the durability of the intervention. Based on findings from these late evaluations, we will re-adapt the tool and process as needed.

#### AIM 3 measures

In the “pre-post” design of this study, Aim 1 measures represent the pre-intervention period and Aim 3 measures represent the post-intervention period. The Aim 3 procedures, therefore, mirror those for Aim 1. The measures are also the same: number of information omissions, handoff accuracy, patient ICU/hospital length of stay and mortality, resource utilization, number of team members present for handoff, handoff duration, quality of teamwork and professionalism (effectiveness); acceptability, appropriateness and feasibility (implementation).

We will also collect data about fidelity, another implementation outcome without a relevant validated measure. Fidelity is generally described as the “faithful” use of a treatment or intervention, or the adherence to the “essential” components of an intervention [28]. For this study, we will create a rating scheme to enable different raters to characterize adherence to elements of the standardized handoff (e.g. team members present, use of a structured form or tool). We will characterize fidelity as the percentage of handoff elements present in a given handoff observation.

### Sample size and power considerations

Qualitative data: Thematic saturation is the point at which additional observations add little or no additional information about the phenomenon of interest [29]. In ethnographic studies, thematic saturation is typically observed after 12–15 observations [30]. Our prior experience suggests that handoffs occurring during the day may materially differ from those conducted at night, so we will collect at least 12 handoffs during the day and 12 during nights and weekends. Additionally, handoffs for patients undergoing elective surgery may be different from patients undergoing emergency surgery. We will also stratify observations by this criterion (Figure 3). Consequently, we expect to reach thematic saturation after observing 48-60 handoffs. The handoffs will be evenly distributed across the two study sites.

**Figure 3 Fig3:**
[figure not shown]
**Handoff observation stratification scheme.**

Quantitative data: As the study is a Type 1 hybrid effectiveness-implementation trial, [16] power calculations are based on our effectiveness hypothesis. Previously published work suggests that, on average, 36-40% of handoff information is omitted in the absence of a standardized handoff process [7, 8]. After institution of a standardized process, information omissions drop by 50-66% [7, 8]. Our handoff observation tool has 13 content items; if our observations are consistent with published work, we will observe 4–5 omissions per handoff episode. We are assuming a standard deviation of 2 information omissions given the heterogeneity of this process, although others have reported a smaller standard deviation [7]. If these assumptions hold true, we will have 95.7% power to detect a drop in information omissions from 4.5 to 3 (a 33% drop), based on a sample size of 96 (48 pre-intervention, 48 post-intervention), and a two-tailed alpha of 0.05. The power calculation suggests that our target sample size for qualitative data will also be sufficient to detect pre- and post- intervention differences in our primary quantitative outcome (Table 3).

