
**Table 2 Tab2:** **Eligible subjects in study population, stratified by study phase**

Study component	Recruitable population*	Target sample size
**Observation (first round)**	440 patients	40-60 patients
	366 clinicians	40-60 handoffs: each consisting of 4-6 clinicians
**Surveys (first round)**	460 clinicians:	460 clinicians
	100 OR nurses	
	100 attending physicians and fellows	
	130 ICU nurses	
	120 residents and CRNAs	
	12 NPs/PAs	
**Interviews (first round)**	12 NPs/PAs	12 NPs/PAs
**Focus groups (first round)**	130 ICU nurses	3 focus groups of 5-8 participants
		(total 15 to 24 ICU nurses)
	120 resident physicians and CRNAs	3 focus groups of 5-8 participants
		(total 15 to 24 residents/CRNAs)
**Simulations**	12 NPs/PAs	4 NPs/PAs (1 per simulation)
	120 residents	8 residents (2 per simulation)
	130 ICU nurses	8 nurses (2 per simulation)
**Observation (second round)**	440 patients	40-60 patients
	366 clinicians	40-60 handoffs consisting of 4-6 clinicians each
**Surveys (second round)**	460 clinicians:	460 clinicians
	100 OR nurses	
	100 attending physicians and fellows	
	130 ICU nurses	
	120 residents and CRNAs	
	12 NPs/PAs	
**Interviews (second round)**	12 NPs/PAs	12 NPs/PAs
**Focus groups (second round)**	130 ICU nurses	2 focus groups of 5-8 participants
		(total 10 to 16 ICU nurses)
	120 resident physicians and CRNAs	2 focus groups of 5-8 participants
		(total 10 to 16 residents/CRNAs)

*Abbreviations: CRNA* certified registered nurse anesthetist, *ICU* intensive care unit, *NP* nurse practitioner, *OR* operating room, *PA* physician assistant.

*Numbers given are estimates, as patient volume and clinician staff numbers are expected to vary over the course of the study.

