### Data analysis

Qualitative approach: We will use a grounded theory approach [22] to develop a codebook and to analyze qualitative data (transcripts from interviews and focus groups, field notes, video recordings). During the analytic process, we will consider how the CFIR constructs described above affect our effectiveness and implementation outcomes. We will also probe for differences between the two study sites that may impact the intervention’s implementation or effectiveness. NVivo 9.0 (QSR International, Doncaster, Victoria, Australia) will be used to manage qualitative data and to facilitate analysis. Qualitative data will be coded by two research personnel; disagreements will be adjudicated by a third person on the research team. We will use the inter-rater reliability function in NVivo to assure consistency in coding within and across coders. Data analysis will start during the data collection for Study Aim 1, allowing us to adjust data collection procedures to adequately explore emerging themes.

Quantitative approach: We will use descriptive statistics to characterize quantitative measures (Table 3). We will stratify our analysis by study unit, time of handoff (day versus night/weekend), elective versus emergency surgery, and surgical specialty. To test the hypothesis about changes in information omissions, we will conduct a Mann–Whitney U test comparing means before and after the intervention. In addition to comparing information omissions within ICUs before and after standardization of the handoff process, we will compare patient outcomes (ICU length of stay, ICU mortality, hospital mortality) in these two study units with contemporary outcomes from two similar non-study units within the same healthcare system. Using a difference-in-differences approach, this latter comparison will enable us to gauge the likelihood that changes in patient outcomes over time were attributable to our intervention or to secular trends. For the quantitative implementation outcomes acceptability and fidelity, we will the Mann Whitney U test to detect site differences in intervention acceptability and fidelity. Quantitative data analyses will be conducted using the Stata program (version 12, StataCorp LLC, College Station, Texas).

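### Table 2 accepts 40 handoffs per observation round, below the 48 per phase behind the stated 95.7% power and below the plan's own 48-60 saturation range

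*Protocol article*

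**What the plan says.** The protocol article gives the number of observed handoffs in three places.

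- *Sample size and power considerations*, qualitative paragraph: "we expect to reach thematic saturation after observing 48-60 handoffs". This follows from a saturation figure of 12 to 15 observations, a minimum of 12 day and 12 night or weekend handoffs, and a further stratification by elective or emergency surgery, for which the text refers to Figure 3.
- The quantitative paragraph of the same section: "95.7% power to detect a drop in information omissions from 4.5 to 3 (a 33% drop), based on a sample size of 96", split as "48 pre-intervention, 48 post-intervention", with "a two-tailed alpha of 0.05". On spread it says: "We are assuming a standard deviation of 2 information omissions given the heterogeneity of this process". It concludes that the qualitative target is also large enough for the primary quantitative outcome.
- *Table 2*, target sample size column: 40 to 60 patients and 40 to 60 handoffs in the first observation round, and the same in the second ("40-60 handoffs consisting of 4-6 clinicians each").

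For the primary comparison, *Data analysis* says: "we will conduct a Mann–Whitney U test comparing means before and after the intervention". The power paragraph does not name the test that it used.

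**The concern.** Table 2 is the only place with a column for the target sample size, and recruiting staff would work from it. Its lower limit is 8 below the number used for power and 8 below the bottom of the saturation range. The statement that the qualitative target also suffices for the primary outcome is supported by a calculation at 48, not at 40.

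At stake is which number ends each observation round. A team that stops at 40 is within Table 2, but the report could then quote a power figure that does not apply to the data collected. *Study status* says that data collection has begun, so the number already matters for the first round. It can still be settled for the second.

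**Working it through.** **Inputs, all from *Sample size and power considerations*:** means 4.5 and 3, so difference d = 1.5; SD s = 2, taken as common to both phases; n = 48 per phase; two-sided alpha 0.05; outcome a count from 0 to 13 ("Our handoff observation tool has 13 content items"). No loss of observations is stated, and none is applied. From Table 2: n = 40 to 60 per round.

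**Step 1: reproduce the plan's figure.** Normal approximation: power = Φ( d / (s·√(2/n)) − 1.96 ).

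n = 48: 1.5 / (2 × √(2/48)) = 1.5 / 0.4082 = 3.674; 3.674 − 1.96 = 1.714; Φ(1.714) = 0.957. This matches the stated 95.7%.

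**Step 2: the same formula across Table 2's range.**

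n = 40: 1.5 / (2 × √(2/40)) = 1.5 / 0.4472 = 3.354; 3.354 − 1.96 = 1.394; Φ(1.394) = 0.918.

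n = 60: 1.5 / (2 × √(2/60)) = 1.5 / 0.3651 = 4.108; 4.108 − 1.96 = 2.148; Φ(2.148) = 0.984.

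**Step 3: does the choice of test matter?** The t-test uses the noncentral t distribution. For Mann-Whitney there are two routes: replacing n by n × 3/π (the asymptotic relative efficiency under normality), and simulation with 20,000 runs per setting, without continuity correction. The shape of the outcome distribution is an assumption, so four were tried.

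| Method | 48 per phase | 40 per phase |
|---|---|---|
| z | 95.7% | 91.8% |
| t-test | 95.3% | 91.2% |
| Mann-Whitney, efficiency 3/π (t to z) | 0.9443 to 0.9485 | 0.8989 to 0.9062 |
| Mann-Whitney, normal | 94.3% | 89.7% |
| Mann-Whitney, normal rounded and clipped to 0-13 | 94.3% | 89.5% |
| Mann-Whitney, beta-binomial on 13 items | 95.7% | 91.2% |
| Mann-Whitney, Poisson (before) and negative binomial (after) | 95.1% | 90.8% |

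The rounded case has SD 1.91 after the intervention, and the Poisson case has SD 2.12 before it. The other two simulated cases have SD 2 in both phases.

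At 48, all results lie within about 1.5 points of the stated figure. Moving from 48 to 40 costs about 4 to 5 points whichever test is used. In terms of the chance of missing the effect, like for like, z goes from 4.3% to 8.2%, and Mann-Whitney goes from 4.3% to 8.8% (beta-binomial) or from 5.7% to 10.3% (normal).

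**Step 4: the hypothesised effect.** *Project aims and hypotheses* expects a 50% drop, so d = 2.25. At n = 40: 2.25 / 0.4472 = 5.031; 5.031 − 1.96 = 3.071; Φ(3.071) = 0.999.

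**Step 5: the strata.** The minimum that the text states in numbers is 12 + 12 = 24, which 40 can meet. If 12 to 15 were needed in each of four cells (day or night/weekend by elective or emergency), the total would be 4 × 12 = 48 to 4 × 15 = 60. That reproduces the stated range at both ends, and 40 would then be 48 − 40 = 8 short.

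**The case against.** The strongest case on the other side is that the power sentence contains no error. It states its own conditions, and under them 95.7% is correct. About 90% at the lower limit is ample, the effect powered for is smaller than the one hypothesised, and the plan notes that others found a smaller SD than 2. All of this stands, and it makes the point a matter of consistency.

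Table 2 also carries a footnote calling its numbers estimates. That does not resolve the conflict, because the asterisk is on the recruitable population column and not on the target column.

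Three stronger readings are tempting, and the document does not support them.

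- *A reader might infer that 95.7% holds only for a z-test and that the planned rank test undermines it.* The exact decimal does come from the z formula. At 48 per phase, though, Mann-Whitney gives about 94% to 96%, and 95.7% under a beta-binomial model, which suits a 13-item count. Replacing the figure with 94% would exchange one assumption-dependent number for another.
- *A reader might infer that 40 handoffs cannot meet a quota of 12 per stratum.* The only numerical quota in the text totals 24. Twelve in each of four cells is a plausible inference from the 48-60 range, but Figure 3, which would confirm it, is not available here.
- *A reader might say that the miss probability rises from 4.3% to about 10%.* That comparison changes the test and the sample size together. The like-for-like changes are those in the working.

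**Conclusion.** The point holds as an internal contradiction. Table 2's lower limit of 40 per round disagrees with the 48-60 of the qualitative rationale and with the 48 per phase of the power statement. At 40 per phase the power for a drop from 4.5 to 3 is 91.8% (z), 91.2% (t) or about 90% (Mann-Whitney, 89.5% to 91.2% in simulation), so the stated 95.7% does not cover the whole stated target.

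This rests on the plan's own means and SD, on a common SD in both phases apart from the small departures noted, and on reading 48-60 as a number per phase. The power paragraph supports that last reading by tying 48 in each phase to the qualitative target. That 40 falls below the saturation range needs no further assumption; a shortfall of 8 against four cells of 12 does.

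The study is not underpowered on its own assumptions, and no conclusion is put at risk. The correction is worth making because the sample size for the primary outcome should have one value.

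**What to change.** Change 40-60 to 48-60 in both observation rows of Table 2, for patients and for handoffs. If 40 per round is truly acceptable, leave the table and add to the power paragraph that power for the drop from 4.5 to 3 is about 90% at 40 per phase, and reconcile 40 with the saturation range.

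The first option costs four table entries, and up to 8 more observed handoffs per round for a team that would have stopped at 40. The second costs a sentence on power, a reconciliation of the saturation range, and a less favourable power figure. Neither changes the design. The 95.7% can stay as the figure for 48 per phase, and nothing here calls for recomputing the sample size before Aim 3.

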### Data analysis

Qualitative approach: We will use a grounded theory approach [22] to develop a codebook and to analyze qualitative data (transcripts from interviews and focus groups, field notes, video recordings). During the analytic process, we will consider how the CFIR constructs described above affect our effectiveness and implementation outcomes. We will also probe for differences between the two study sites that may impact the intervention’s implementation or effectiveness. NVivo 9.0 (QSR International, Doncaster, Victoria, Australia) will be used to manage qualitative data and to facilitate analysis. Qualitative data will be coded by two research personnel; disagreements will be adjudicated by a third person on the research team. We will use the inter-rater reliability function in NVivo to assure consistency in coding within and across coders. Data analysis will start during the data collection for Study Aim 1, allowing us to adjust data collection procedures to adequately explore emerging themes.

Quantitative approach: We will use descriptive statistics to characterize quantitative measures (Table 3). We will stratify our analysis by study unit, time of handoff (day versus night/weekend), elective versus emergency surgery, and surgical specialty. To test the hypothesis about changes in information omissions, we will conduct a Mann–Whitney U test comparing means before and after the intervention. In addition to comparing information omissions within ICUs before and after standardization of the handoff process, we will compare patient outcomes (ICU length of stay, ICU mortality, hospital mortality) in these two study units with contemporary outcomes from two similar non-study units within the same healthcare system. Using a difference-in-differences approach, this latter comparison will enable us to gauge the likelihood that changes in patient outcomes over time were attributable to our intervention or to secular trends. For the quantitative implementation outcomes acceptability and fidelity, we will the Mann Whitney U test to detect site differences in intervention acceptability and fidelity. Quantitative data analyses will be conducted using the Stata program (version 12, StataCorp LLC, College Station, Texas).

Mixed methods approach: We will convene at least three members of the research team to characterize observed handoffs in Aims 1 and 3 as “satisfactory” or “unsatisfactory” on the basis of field notes and data from our handoff checklists. Once handoffs have been categorized in this way, we will re-analyze our quantitative outcomes (mortality, length of stay, resource utilization, etc.), stratifying them by the quality of handoff. We will perform this analysis with Aim 1 data alone to study the relationship between “good” handoffs and patient outcomes in the absence of a standard handoff process, and will also perform this analysis again once we have Aim 3 data.

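### Handoffs are sampled by unit, time of day and urgency, but the only test named for the primary omissions outcome is an unstratified Mann–Whitney U, and the announced stratification is not tied to it

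*Protocol article*

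**What the plan says.** **Sampling** (Sample size and power considerations, Qualitative data). The protocol reports prior experience that "handoffs occurring during the day may materially differ from those conducted at night" and sets a minimum of 12 handoffs for daytime and 12 for nights and weekends. It says elective and emergency cases may also differ: "We will also stratify observations by this criterion". On units: "The handoffs will be evenly distributed across the two study sites". The expected total is 48 to 60 handoffs; Table 2 gives 40 to 60 per round. AIM 3 measures says that the post-intervention procedures mirror those of Aim 1.

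**Power** (same section, Quantitative data). "We are assuming a standard deviation of 2 information omissions", with a fall from 4.5 to 3 omissions, "a sample size of 96 (48 pre-intervention, 48 post-intervention), and a two-tailed alpha of 0.05", and 95.7% power. Strata do not enter the calculation.

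**Analysis** (Data analysis, Quantitative approach). After a sentence on descriptive statistics, the protocol says its analysis will be stratified by unit, time of handoff, urgency and surgical specialty. The next sentence names the primary before/after test: "To test the hypothesis about changes in information omissions, we will conduct a Mann–Whitney U test". The one after that refers to the omissions comparison as being within ICUs. No sentence says whether the stratification means a stratified primary test, a separate test in each stratum, or descriptive results by subgroup.

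**The concern.** When a sample is built to the same strata in both periods and those strata affect the outcome, the stratum differences cancel from the before/after contrast. A pooled test still counts them as noise. Its p-value is then too large on average, and it can miss a real reduction that a stratified test would find.

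When the strata are not filled in the same proportions in both periods, the pooled contrast picks up the change in mix. This matters more here than in a randomised trial. The Discussion acknowledges that a pre-post design has no true control, and the difference-in-differences comparison with non-study units covers patient outcomes, not omissions.

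The possible readings of the stratification sentence also lead to materially different tests, and the choice should not remain open once post-intervention data are in hand.

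**Working it through.** **1. Reproduce the stated power.** Inputs from the protocol: difference 4.5 − 3 = 1.5, SD 2, 48 per period, two-sided alpha 0.05.

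- SE = 2 × √(2/48) = 0.408; 1.5/0.408 = 3.674; power = Φ(3.674 − 1.960) = Φ(1.714) = 95.7%.
- This matches the stated figure, so the calculation is for the pooled comparison with the total SD. (Scaling n by the Mann–Whitney efficiency 3/π gives 94.9%.)

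**2. What each reading of the stratification sentence implies.**

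- Results by subgroup only: the primary test is the pooled one.
- A separate test in each stratum: the stated power does not apply. By the same formula, 24 v 24 gives Φ(2.598 − 1.960) = 74% and 12 v 12 gives Φ(1.837 − 1.960) = 45%.
- One stratified test: this is the fix below and only needs to be stated.

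**3. Cost of pooling when the mix is equal.** Two assumptions are needed.

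- R², the share of outcome variance explained by the sampling factors. The protocol gives no figure; the range used is 0 to 0.30.
- Eight equal cells (unit × time × urgency) of 6 handoffs per period. This fits 4 × 12 = 48 split evenly over two units, but the figure with the scheme is not shown.

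Formulas (normal approximation): residual SD = 2√(1 − R²); true type I error of the pooled test = 2Φ(−1.96/√(1 − R²)); adjusted 95% half-width = 1.96 × residual SD × √(2/48).

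| R² | Residual SD | Pooled type I error | Adjusted half-width |
|---|---|---|---|
| 0 | 2.00 | 5.0% | 0.80 |
| 0.10 | 1.90 | 3.9% | 0.76 |
| 0.20 | 1.79 | 2.8% | 0.72 |
| 0.30 | 1.67 | 1.9% | 0.67 |

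Simulation (20,000 runs per setting; normal values rounded and clipped to 0–13; equal additive effects of the three factors), plain Mann–Whitney v van Elteren stratified rank test:

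| R² | Type I error | Power, drop 1.0 | Power, drop 1.5 |
|---|---|---|---|
| 0 | 4.9% v 5.0% | 65.2% v 63.5% | 93.9% v 92.7% |
| 0.10 | 3.7% v 4.9% | 66.2% v 67.8% | 94.9% v 95.3% |
| 0.20 | 2.8% v 4.8% | 65.7% v 71.9% | 95.6% v 96.8% |
| 0.30 | 2.2% v 5.2% | 67.1% v 78.4% | 96.7% v 98.2% |

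The gain from stratifying starts at an R² of roughly 0.05 to 0.10.

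**4. How large must the stratum effects be?** With three equal binary factors, the between-stratum variance is 4R², or 4R²/3 per factor, so the two levels of each factor differ by 2√(4R²/3). This is 0.73 omissions at R² 0.10, 1.03 at 0.20 and 1.26 at 0.30.

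**5. Unequal mix, an illustration.** Suppose one quarter of the sample, such as night/weekend emergency cases over both units, has 12 of 48 handoffs before (25%) and 24 of 60 after (40%), and its mean differs by 1.5 from the rest. The pooled difference moves by (0.40 − 0.25) × 1.5 = 0.225 omissions, or 15% of the planned 1.5. Putting all 12 extra handoffs in one group is a worst case. The direction depends on which group is over-filled and whether it has more or fewer omissions.

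**The case against.** The strongest reply is that the protocol does not ignore the strata. The sentence directly before the test announces stratification by these same factors, and the sentence after it describes the omissions comparison as within ICUs. A condensed article may leave the mechanics to an analysis plan that is not shown. This stands against a reader who infers that stratification was forgotten. What remains is that the article does name a primary test, that test is the unstratified one, and the power figure matches it.

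Three further inferences are tempting and not supported:

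- *That the plan expects the groups to differ in omissions.* It says only that they may differ, it gives that reason for time and urgency but not for unit, and it does so under qualitative saturation. No effect on the omission count is stated.
- *That the p-value is too large.* This holds only if the factors predict omissions and the mix is equal. At R² = 0 there is no conservatism, and van Elteren loses 1 to 2 points of power. The 0.30 case needs each factor to shift omissions by 1.26, which is 84% of the planned drop.
- *That the primary result would be invalid.* A conservative test is still valid, and the protocol names no confidence interval that could be called wrong.

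The effect-size argument also carries weight. The stated hypothesis is a 50% fall, from 4.5 to 2.25. At 48 v 48 and SD 2, normal-approximation power for that is about 99.98% without adjustment. The efficiency loss matters mainly if the true drop is well below plan.

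**Conclusion.** The point holds as one of efficiency, protection against a shift in mix, and clarity. The sampling uses unit, time and urgency; the named primary test does not; and the announced stratification is not connected to it.

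For R² between 0.10 and 0.30 over eight equal cells, both assumed, pooling lowers the type I error to about 4% to 2%. It costs about 2 to 11 points of power for a drop of 1.0, but only about 0.5 to 2 points for the planned 1.5. At R² 0.20 the adjusted interval is about 11% narrower (0.72 against 0.80).

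The risk from an unequal mix is separate and can go either way. It is real because the time-of-day quotas are minimums and the totals are ranges, but its size cannot be known in advance. The pooled test stays valid when the mix is the same in both periods.

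**What to change.** State in Data analysis that the primary pre/post comparison of omissions is stratified by, or adjusted for, the three sampling factors (unit, day versus night/weekend, elective versus emergency). A van Elteren test over the sampling cells would do, as would a regression with these factors as terms. Report the adjusted before/after difference with its 95% interval. Keep the pooled Mann–Whitney as a supporting analysis. Keep surgical specialty descriptive, since it is not among the sampling factors described in the text.

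The cost is one sentence, with no new data and no larger sample. If the factors turn out not to matter, van Elteren in cells of 6 + 6 loses about 1 to 2 points of power. A main-effects regression loses essentially none: three extra terms take the residual degrees of freedom from 94 to 91. The choice should be fixed before post-intervention omissions are analysed.
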